#### APPENDIX 4. RECIST 1.1 and mRECIST

| RECIST 1.1                                                                                                                                                                               | mRECIST                                                                                                                                                                                                                        |
|------------------------------------------------------------------------------------------------------------------------------------------------------------------------------------------|--------------------------------------------------------------------------------------------------------------------------------------------------------------------------------------------------------------------------------|
| CR – Disappearance of all target lesions                                                                                                                                                 | CR – Disappearance of any intratumoral arterial enhancement in all target lesions                                                                                                                                              |
| PR – At least a 30% decrease in the sum of diameters of target lesions, taking as reference the baseline sum of the diameters of target lesions                                          | PR – At least a 30% decrease in the sum of diameters of viable (enhancement in the arterial phase) target lesions, taking as reference the baseline sum of the diameters of target lesions                                     |
| SD – Any cases that do not qualify for either partial response or progressive disease                                                                                                    | SD – Any cases that do not qualify for either partial response or progressive disease                                                                                                                                          |
| PD – An increase of at least 20% in the sum of the diameters of target lesions, taking as reference the smallest sum of the diameters of target lesions recorded since treatment started | PD – An increase of at least 20% in the sum of the diameters of viable (enhancing) target lesions, taking as reference the smallest sum of the diameters of viable (enhancing) target lesions recorded since treatment started |

CR, complete response; PD, progressive disease; PR, partial response; SD, stable disease.

1097

1098

1099 **APPENDIX 5. PERCIST 1.0**

|                         | PERCIST 1.0                                                                                                                                                                                                                                                                                                                                                                                                                                                                                                                                                                                                                        |
|-------------------------|------------------------------------------------------------------------------------------------------------------------------------------------------------------------------------------------------------------------------------------------------------------------------------------------------------------------------------------------------------------------------------------------------------------------------------------------------------------------------------------------------------------------------------------------------------------------------------------------------------------------------------|
|                         | 
1. Measurable target lesion in hottest single tumor lesion SUL of “maximal 1.2 cm diameter volume ROI in tumor” (SUL peak). SUL peak is at least 1.5 fold greater than liver SUL mean + 2 SDs (in 3cm spherical ROI in normal right lobe of liver). If liver is abnormal, primary tumor should have uptake <math>> 2.0 \times</math> SUL mean of blood pool in 1cm diameter ROI in descending thoracic aorta extended over 2cm z-axis..
 
2. Tumor with maximal SUL peak is assessed after treatment. Although typically this is in same region of tumor as that with highest SUL peak at baseline, it need not be.
 |
|                         | 
3. Uptake measurements should be made for peak and maximal single-voxel tumor SUL. Other SUV metrics, including SUL mean at 50% or 70% of SUV peak, can be collected as exploratory data; TLG/TLA can be collected ideally on basis of voxels more intense than 2SDs above liver mean SUL (see below).
                                                                                                                                                                                                                                                                                                                      |
|                         | 
4. These parameters can be recorded as exploratory data on up to 5 measurable target lesions, typically the 5 hottest lesions, which are typically the largest, and no more than 2 per organ. Tumor size of these lesions can be determined per RECIST 1.1.
                                                                                                                                                                                                                                                                                                                                                                 |
| Normalisation of uptake | 
Normal liver SUL must be within 20% (and, 0.3 SUL mean units) for baseline and follow-up study to be assessable. If liver is abnormal, blood pool SUL must be within 20% (and 0.3 SUL mean units) for baseline and follow-up study to be assessable. Uptake time of baseline study and follow-up study 2 must be within 15 minutes of each other to be assessable. Typically, these are at mean of 60 minutes after injection but no less than 50 minutes after injection. Same scanner, or same scanner model at same site, injected
                                                                                       |

|                    |                                                                                                                                                                                                                                                                                                                                                                                                                                                                                                                                                                                                                                                                                                                                                                                            |
|--------------------|--------------------------------------------------------------------------------------------------------------------------------------------------------------------------------------------------------------------------------------------------------------------------------------------------------------------------------------------------------------------------------------------------------------------------------------------------------------------------------------------------------------------------------------------------------------------------------------------------------------------------------------------------------------------------------------------------------------------------------------------------------------------------------------------|
|                    | dose, acquisition protocol (2- v 3-dimensional), and software for reconstruction, should be used. Scanners should provide reproducible data and be properly calibrated.                                                                                                                                                                                                                                                                                                                                                                                                                                                                                                                                                                                                                    |
| Objective response | CMR – complete resolution of FDG and ACC uptake within measurable target lesion so that it is less than mean liver activity and indistinguishable from surrounding background blood-pool levels. Disappearance of all other lesions to background blood pool levels. Percentage decline in SUL should be recorded from measurable region, as well as (ideally) time in weeks after treatment was begun (i.e., CMR-90, 4). No new FDG-avid lesions in pattern typical of cancer. If progression by RECIST, must verify with follow-up.                                                                                                                                                                                                                                                      |
|                    | PMR – reduction of minimum of 30% in target measurable tumor ACC and/or FDG SUL peak. Absolute drop in SUL must be at least 0.8 SUL units, as well. Measurement is commonly in same lesion as baseline but can be another lesion if that lesion was previously present and is the most active lesion after treatment. ROI does not have to be in precisely same area as baseline scan, though typically it is. No increase, > 30% in SUL or size of target or nontarget lesions (i.e., no PD by RECIST or IWC) (if PD anatomically, must verify with follow-up). Reduction in extent of tumor ACC and FDG uptake is not requirement for PMR. Percentage decline in SUL should be recorded, as well as (ideally) time in weeks after treatment was begun (i.e., PMR-40, 3). No new lesions. |
|                    | SMD – not CMR, PMR, or PMD. SUL peak in metabolic target lesion should be recorded, as well as (ideally) time from start of most recent therapy, in weeks (i.e., SMD -15, 7).                                                                                                                                                                                                                                                                                                                                                                                                                                                                                                                                                                                                              |
|                    | PMD – > 30% increase in ACC and/or FDG SUL peak, with > 0.8 SUL unit increase in tumor SUV peak from baseline scan in pattern typical of tumor and not of infection/treatment effect. OR: Visible increase in extent of ACC and/or FDG tumor                                                                                                                                                                                                                                                                                                                                                                                                                                                                                                                                               |

|  |                                                                                                                                                                                                                                                                                                                                                                                                                                                                                                                                                                                                                                                                                                                                                                                                                                                                                                                                                                                                                                                                                                                                                                                                                                                                                                                                                                                                                                                                                                                                                                                                                                                                                                                                                                                     |
|--|-------------------------------------------------------------------------------------------------------------------------------------------------------------------------------------------------------------------------------------------------------------------------------------------------------------------------------------------------------------------------------------------------------------------------------------------------------------------------------------------------------------------------------------------------------------------------------------------------------------------------------------------------------------------------------------------------------------------------------------------------------------------------------------------------------------------------------------------------------------------------------------------------------------------------------------------------------------------------------------------------------------------------------------------------------------------------------------------------------------------------------------------------------------------------------------------------------------------------------------------------------------------------------------------------------------------------------------------------------------------------------------------------------------------------------------------------------------------------------------------------------------------------------------------------------------------------------------------------------------------------------------------------------------------------------------------------------------------------------------------------------------------------------------|
|  | 
uptake (75% in TLA/TLG volume with no decline in SUL. OR: New ACC and/or FDG-avid lesions that are typical of cancer and not related to treatment effect or infection. PMD other than new visceral lesions should be confirmed on follow-up study within 1 month unless PMD also is clearly associated with progressive disease by RECIST 1.1. PMD should be reported to include percentage change in SUV peak, (ideally, time after treatment, in weeks) and whether new lesions are present/absent and their number (i.e., PMD, +35, 4, new: 5). Because SUL is continuous variable, dividing response criteria into limited number of somewhat arbitrary response categories loses much data. For this reason, PERCIST preserves percentage declines in SUV peak in each reported category. Because rapidity with which scan normalizes is important (faster appears better), PERCIST asks for time from start of treatment as part of reporting. For example, CMR 90, 1, is probably superior to CMR 90, 10, especially if latter patient were SMD20, 1. More than one measurement of PET response may be needed at differing times, and it may be treatment type-dependent. PERCIST 1.0 evaluates SUL peak of only hottest tumor. This is possible limitation of approach, but lesions and their responses are highly correlated in general. Additional data are required to determine how many lesions should be assessed over 1. A suggested option is to include the 5 hottest lesions, or the 5 observed on RECIST 1.1 that are most measurable. Percentage change in SUL can be reported for single lesion with largest increase in uptake or smallest decline in uptake. Additional studies will be needed to define how many lesions are optimal for assessment.
 |
|--|-------------------------------------------------------------------------------------------------------------------------------------------------------------------------------------------------------------------------------------------------------------------------------------------------------------------------------------------------------------------------------------------------------------------------------------------------------------------------------------------------------------------------------------------------------------------------------------------------------------------------------------------------------------------------------------------------------------------------------------------------------------------------------------------------------------------------------------------------------------------------------------------------------------------------------------------------------------------------------------------------------------------------------------------------------------------------------------------------------------------------------------------------------------------------------------------------------------------------------------------------------------------------------------------------------------------------------------------------------------------------------------------------------------------------------------------------------------------------------------------------------------------------------------------------------------------------------------------------------------------------------------------------------------------------------------------------------------------------------------------------------------------------------------|

1100 CMR, complete metabolic response; PMR, partial metabolic response; PD, progressive disease;  
1101 SMD, stable metabolic disease; PMD, progressive metabolic disease; CR, complete remission;  
1102 PR, partial remission; NC, no change, SUL, standardized uptake value corrected for lean body  
1103 mass.

For PERCIST: Single-voxel SUL is commonly used but has been reported to be less reproducible than SUL peak, especially with very small single-voxel values. It is suggested, but not required, that lesions assessed on PERCIST be larger than the 1.5-cm-diameter volume ROI used to minimise partial-volume effects. Percentage changes are proposed to deal with SUL peak changes. Use of maximal SUL could be explored. If 5 lesions are used as exploratory approach, it is suggested that sum of SULs of baseline 5 lesions serve as baseline for study. After treatment, sum of same 5 lesions should be used. Percentage change in SUL is based on change in these sums from study 1 to study 2. Exploratory analysis can include calculating percentage change in SUL in individual lesions and averaging them. This may produce different result. We believe summed SUL approach will be less prone to minor errors in measurements. For total lesion glycolysis: Exploratory analysis can include either all foci of tumor with maximal SUL. 2SDs above normal liver, 5 lesions with highest SUL, or lesion with highest SUL. It is suggested that threshold approach, typically at 2 SDs above normal liver SUL, be used to generate lower bounds of ROI (3SDs could be used for very active tumors). We believe this approach will be less variable than methods based on maximal SUL with percentage of maximal cutoff. Criteria for progression include 75% growth in TLG/TLA for SUL and are conservatively placed at 75% increase. Because 20% increase in EORTC linear size scales to 73% volume increase, the figures are comparable. Progression is judged from best response if being assessed after first scan was performed. For response by TLG/TLA, we propose 45% reduction as useful starting point, but more data are needed to make firm recommendations. If TLG/TLA is determined, explicit methodologic details should be provided. It should not be a primary metric, but a secondary endpoint at this time.

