### **1.1.4 Dual-tracer positron-emission tomography with integrated computed tomography (PET-CT)**

PET-CT with 18F-fluorodeoxyglucose (FDG) has also been evaluated in HCC diagnosis and surveillance after treatment. However, FDG is just able to detect poorly differentiated HCC only. Dual-tracer (11C-acetate [ACC] and 18F-fluorodeoxyglucose [FDG]) positron-emission tomography with integrated CT (PET-CT) was proven more sensitive and specific than FDG-alone PET-CT in HCC diagnosis and surveillance. In particular, dual-tracer PET-CT was found superior than contrast-enhanced CT scan in diagnosing and selecting

patients for LT, so that the liver grafts were given only to those who really fulfilled the LT criteria.

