# **3. ELIGIBILITY CRITERIA**

## **3.1 Inclusion Criteria**

1. Patients must have histologically or radiologically confirmed HCC not amenable to curative resection. For radiological diagnosis of HCC, a contrast-enhanced computed tomography or magnetic resonance imaging is mandatory to demonstrate the early arterial enhancement in arterial phase and contrast washout in the porto-venous phase on the imaging.
2. Capable of giving signed informed consent which includes compliance with the requirements and restrictions listed in the informed consent form (ICF) and in this protocol. Written informed consent and any locally required authorization (e.g. Health Insurance Portability and Accountability Act in the US, European Union [EU] Data Privacy Directive in the EU) obtained from the patient/legal representative prior to performing any protocol-related procedures, including screening evaluations.

- 191
- 192 3. HCC lesions within University of California, San Francisco (UCSF) criteria for LT
- 193 (solitary tumor  $\leq 6.5\text{cm}$ , up to 3 tumors with none  $> 4.5\text{cm}$ , and total tumor diameter
- 194  $\leq 8\text{cm}$ ).
- 195
- 196 4. Be  $\geq 18$  years of age on day of signing informed consent.
- 197
- 198 5. Have a performance status of 0 to 2 on the Eastern Cooperative Oncology Group
- 199 (ECOG) Performance Scale.
- 200 6. A stage C or earlier HCC based on Barcelona Clinic Liver Cancer (BCLC) staging
- 201 system.
- 202 7. A Child-Pugh score of B8 or less.
- 203
- 204 8. Demonstrate adequate organ function as defined in Inclusion Criteria 7, all screening
- 205 labs should be performed 28 days prior to study registration up to the first dose of
- 206 study drug.
- 207
- 208 9. Adequate serum hematological functions defined as:
- 209 - Absolute neutrophil count (ANC)  $\geq 1.0 \times 10^9/\text{l}$
- 210 - Platelet  $\geq 20 \times 10^9/\text{l}$
- 211 - Hemoglobin  $\geq 8 \text{ g/dl}$
- 212 Adequate serum biochemistry functions defined as:
- 213 - Serum bilirubin  $\leq 5.0 \times$  institutional upper limit of normal (ULN). <<This will
- 214 not apply to patients with confirmed Gilbert's syndrome (persistent or recurrent
- 215 hyperbilirubinemia that is predominantly unconjugated in the absence of hemolysis
- 216 or hepatic pathology), who will be allowed only in consultation with their
- 217 physician.>>
- 218 - AST (SGOT)/ALT (SGPT)  $\leq 6.0 \times$  institutional upper limit of normal unless liver

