## 8. STATISTICAL PLAN

The sample size for this phase 2 study is based on the following assumptions:

The primary endpoint is progression-free survival.

The following hypotheses are used:

- $p_0=60\%$ , assumed objective response after TACE or RFA as bridging therapy
- $p_1=85\%$ , expected objective response after SBRT as bridging therapy

With a two-sided alpha value of 0.05 and an 80% power of detection of statistical significance, 28 patients were required. Assuming a dropout rate of about 20%, 35 patients were required for eligibility screening in this study.

Kaplan-Meier methods are used for survival analysis. Log-rank tests are performed for comparison of survival among different patient subgroups. Cox regression with univariable and multivariable analyses are performed for prognostic factors PFS and OS.

All statistical analyses are performed by Statistical Package for Social Sciences (SPSS) version 24, or R 3.6.1 or more advanced versions. Statistical significance is defined as  $P$  value  $< .05$  (two-sided).

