1051 begins with non-contrast whole-body CT for attenuation correction, followed by PET with a 2-  
1052 minute emission acquisition time and a 16.2-cm axial field of view per position. At 45 minutes  
1053 after ACC injection, 330-520 MBq (6.3 MBq/kg of body weight) FDG was injected and the  
1054 same image acquisition was obtained at 60 minutes after FDG administration. Enhanced (with  
1055 Omnipaque 300, 2ml/kg; GE Healthcare) CT scanning with an in-house 3-phase (early and late  
1056 arterial and porto-venous) contrast-enhanced protocol covering the whole abdomen was then  
1057 performed for additional diagnostic evaluation. All HCC lesions were evaluated by two  
1058 independent radiologists and any discrepancy in determining the nature of the lesions was  
1059 solved by consensus.

1060 **Determination of MTV and TLG/TLA**

1061 Firstly, spherical volume of interests (VOI) with a diameter of 3cm were positioned in the right  
1062 lobe of liver at least 3 cm away from the tumors (if present) or the mediastinal blood pool if the  
1063 VOI cannot be reliably placed in the liver without being interfered by the adjacent tumor lesions  
1064 to determine the background standardized uptake value (SUV) as reference. The mean SUV  
1065 and standard deviation (SD) of these VOIs based on FDG and ACC were calculated and  
1066 recorded as  $SUV_{ref}$  and  $SD_{ref}$  respectively. For those patients whose lesion was seen with only 1  
1067 type of radiotracer, the same ROI was applied at the same level on the axial images of the other  
1068 radiotracer, correcting for any misalignment or misregistration of present. Background threshold  
1069 method was used to determine the threshold for subsequent delineation of the MTV as follows:  
1070  $Threshold = SUV_{ref} + 2SD_{ref}$ . TLG with respect to FDG or TLA with respect to ACC of any  
1071 tumor lesions is the product of  $SUV_{mean}$  and MTV of that lesion with respect to each  
1072 radiotracer. Only lesions that could be delineated using the threshold were deemed reportable  
1073 and were further measured using automatic segmentation using a GE advantage workstation.  
1074  $SUV_{max}$ , MTV and TLG/TLA were then computed. Lesions with metabolic activities less than  
1075 these threshold will be considered as “non-reportable”, and therefore “normal”. All these  
1076 parameters will be recorded as zero.

1077

1078

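### Two response definitions for the co-primary endpoint (mRECIST partial response, PERCIST complete metabolic response) conflict with neighbouring rows and, read literally, can score a non-responder as a responder

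*Protocol*

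**What the plan says.** Protocol sections 2.1 and 8.1.1 list best objective response by RECIST 1.1, mRECIST and PERCIST among the primary endpoints, and the Synopsis calls it co-primary with progression-free survival. Section 6.5 sends the reader to Appendices 4 and 5 for the definitions, so these tables are the operative rules.

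- **mRECIST, Appendix 4.** The partial-response row asks for "PR – At least a 30% decrease in the sum of diameters of viable (enhancement in the arterial phase) target lesions". Its reference is the baseline sum of target-lesion diameters, with no restriction to viable tumour. The progression row restricts both sides of the comparison to viable (enhancing) diameters.
- **PERCIST, Appendix 5.** Complete metabolic response (CMR) requires uptake of both FDG and 11C-acetate (ACC) to resolve in the measurable target, but its new-lesion condition reads "No new FDG-avid lesions in pattern typical of cancer". Partial metabolic response (PMR) bars any new lesion. Progressive metabolic disease (PMD) includes "New ACC and/or FDG-avid lesions that are typical of cancer and not related to treatment effect or infection".
- **Role of the two tracers, section 1.1.4.** "FDG is just able to detect poorly differentiated HCC only", which is the protocol's reason for adding acetate.
- **Sample size, section 8.** It rests on response rates of 60% ("assumed objective response after TACE or RFA as bridging therapy") and 85% ("expected objective response after SBRT as bridging therapy").

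**The concern.** Response categories should be mutually exclusive, and each should compare like with like. The mRECIST partial-response row compares viable diameter after treatment with total diameter before it. A lesion that was partly non-enhancing from the start can therefore pass the 30% threshold without shrinking. In PERCIST the best category carries a weaker new-lesion condition than the next one down, and it overlaps with progression.

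The trial has one arm and judges its response rate against a fixed 60%, so no control group absorbs a scoring error. Because the endpoint is best response, a response label earned on one scan is kept. Progression also defines the other co-primary endpoint, so a scan that meets both categories could count as a response in one analysis and an event in the other.

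**Working it through.** **1. The plan's own figure.** Inputs from section 8: p0 = 0.60, p1 = 0.85, two-sided alpha 0.05, power 80%, N = 28, and 35 after 20% dropout. One-sample normal approximation:

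n = (1.960 × √(0.60 × 0.40) + 0.842 × √(0.85 × 0.15))² / 0.25² = 25.4, so 26. With continuity correction it is 29.3, so 30.

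The stated 28 lies between the two, and 28/(1 − 0.20) = 35 exactly. The repairs below concern definitions and leave N unchanged.

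**2. mRECIST partial response.** Let T be the baseline total diameter, v0 the baseline enhancing diameter and v1 the enhancing diameter at follow-up. The literal rule gives (v1 − T)/T. Viable against viable gives (v1 − v0)/v0. The sizes below are assumed. For progression, v0 is taken as the smallest viable sum recorded.

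| T (mm) | v0 | v1 | As written | Viable vs viable |
|---|---|---|---|---|
| 50 | 50 | 50 | 0%, stable | 0%, stable |
| 50 | 40 | 40 | −20%, stable | 0%, stable |
| 50 | 35 | 35 | −30%, partial response | 0%, stable |
| 50 | 30 | 35 | −30%, partial response | +16.7%, stable |
| 50 | 25 | 30 | −40%, partial response | +20%, progression |

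- An unchanged lesion (v1 = v0) is a literal partial response when v0/T ≤ 0.70.
- Literal partial response and progression coincide when v1 ≤ 0.70T and v1 ≥ 1.20v0. This is possible once v0 ≤ (0.70/1.20)T = 0.583T.
- Suppose the lesion in the last row is unchanged at 3 months and grows by 6 months. The 3-month scan is already (25 − 50)/50 = −50%, a literal partial response. A precedence rule at 6 months would not undo it, so the reference itself has to be corrected.

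**3. PERCIST new lesions.**

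| Category | Treatment of new lesions |
|---|---|
| CMR | FDG-avid lesions barred; acetate-only not mentioned |
| PMR | any new lesion barred |
| PMD | acetate- and/or FDG-avid lesions count |

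Take a target cleared on both tracers and a new acetate-only liver lesion typical of cancer. The CMR target condition and the CMR new-lesion condition as written are both met. PMR is not available, because there is a new lesion. PMD is met, and Appendix 5 exempts new visceral lesions from its confirmation step. No sentence says which category stands. By section 1.1.4, acetate-only lesions are foreseeable.

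**4. Size.** One patient in 28 is 3.6 percentage points on the criterion affected. For illustration only, assume the 60% test is run on that criterion with an exact binomial rule. Success then needs at least 23 of 28 (upper tail 1.1% at a true 60%). If an assumed share of true non-responders is scored as responders, the chance of false success becomes:

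| Share mis-scored | Observed rate | False success |
|---|---|---|
| 0% | 60% | 1.1% |
| 10% | 64% | 3.1% |
| 20% | 68% | 7.6% |

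The documents give no share, and they do not say which criterion carries the test.

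**The case against.** **What tells against the point**

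- The partial-response row speaks of a decrease in the viable sum, and an unchanged lesion has none. On that reading the reference is viable by implication. This is a fair reading, but the row does not say so, and the progression row shows the restriction being written out when it was meant.
- Section 3.2 excludes prior resection, prior locoregional therapy and prior radiation to the treated area. Many lesions may therefore enhance throughout, and total and viable diameters may be close. This stands, and it limits the frequency.
- CMR also requires all other lesions to fade to background, and the hottest tumour after treatment need not be the baseline one. These conditions narrow the gap without closing it. The first fits lesions already known, and the PMR row limits a change of measured lesion to one previously present. PMD does count new acetate-avid lesions, so the fault is an unresolved overlap; such lesions are not overlooked altogether.

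**Stronger readings a reader might infer, which the documents do not support**

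- *A lesion without baseline uptake is automatically CMR.* CMR refers to a measurable target, and Appendix 5 sets an uptake threshold for that, so such a patient is not assessable by PERCIST. The Appendix 3 rule that faint lesions "will be considered as “non-reportable”, and therefore “normal" belongs to the metabolic-volume measures, which section 6.5 treats as exploratory.
- *A histologically proven, non-enhancing tumour is mRECIST complete response at every scan.* Entry does allow this route ("Patients must have histologically or radiologically confirmed HCC not amenable to curative resection"), with enhancement mandatory only for radiological diagnosis. But disappearance of enhancement is fairly read as needing enhancement to begin with.
- *Every gap errs towards response.* A patient with no PERCIST-measurable lesion cannot reach PMR, so the direction is not uniform.

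**Conclusion.** Wrong as written, in two places. The mRECIST partial-response reference does not match the progression row. The CMR new-lesion condition does not match PMR or PMD. Followed literally, either row can label a non-responder a responder, and either can put one scan in both response and progression with no rule to decide.

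The mRECIST conclusion rests on reading the row literally and on some lesions enhancing over no more than 70% of their baseline diameter. The PERCIST conclusion rests on new acetate-only lesions occurring after the target clears. Neither frequency is in the documents, so no total bias in the response rate can be stated; the false-success figures show sensitivity to assumed shares only. An mRECIST error does not move the RECIST 1.1 or PERCIST rate. The case for repair is that these definitions govern a co-primary endpoint and cost little to put right.

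**What to change.** 1. **Appendix 4, mRECIST partial response:** set the reference to the baseline sum of viable (enhancing) target-lesion diameters, matching the progression row.
2. **Appendix 5, CMR:** change the new-lesion condition to no new FDG- and/or ACC-avid lesions in a pattern typical of cancer.
3. **Both appendices:** state that PD or PMD takes precedence when one scan also meets a response category.
4. **Not evaluable:** class patients with no arterially enhancing lesion at baseline as not evaluable by mRECIST, and those with no lesion meeting the Appendix 5 threshold as not evaluable by PERCIST. Report their number for each criterion.

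No new inclusion criterion is needed, and N stays at 28. The cost is a short amendment, a check that any scans already read follow the corrected rows, and possibly fewer evaluable patients by mRECIST or PERCIST, shown openly in the report.
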